### Neuropsychological assessment

A set of neuropsychological tests will be used to assess cognitive function and behavior of all the participants, and their activities of daily living will also be measured. The assessments will be performed at baseline, 4-week treatment, and 4-week post-treatment follow-up.

The Chinese version of the Montreal Cognitive Assessment Basic (MoCA-B) is a cognitive function screening tool tailored for individuals with low educational attainment, demonstrating high cultural adaptability (Chen et al., 2016; Julayanont et al., 2015). The total score is 30 points, with a score of ≥ 26 indicating normal cognitive function and a score of ≤ 26 suggesting impaired cognitive function. The cutoff scores for identifying MCI are adjusted according to the number of years of education: ≤ 19 points for those with ≤ 6 years of education, ≤ 22 points for those with 7-12 years of education, and ≤ 24 points for those with > 12 years of education.

The Rivermead Behaviour Memory Test (RBMT) is a behavioral memory assessment tool developed by the Rivermead Rehabilitation Centre in Oxford, England. It primarily evaluates patients’ memory function and consists of 12 items (Wilson et al., 1989). The total score is 24 points. The grading standards are as follows: 0–9 points indicate severe memory impairment, 10–16 points indicate moderate impairment, 17–21 points indicate mild impairment, and 22–24 points indicate normal memory function.

Modified Barthel Index (MBI) is used to assess the patient’s activities of daily living, including 10 items, including grooming, bathing, eating, toileting, and dressing (Mahoney and Barthel, 1965). The scoring standard is as follows: 100 were completely independent; 95–75 were classified as mild dysfunction; 70–50 were classified as moderate dysfunction; 50–25 were classified as severe dysfunction and obvious life dependence; ≤ 20 was totally dependent in life.

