### Sample size calculation

The sample size was calculated using Power Analysis and Sample Size software version 15.0 (NCSS, LLC). The Factorial analysis of variance test is used for the sample size calculation of four groups. By referring to the previous literature (Wang et al., 2022). on rTMS or taVNS in the treatment of MCI, rTMS stimulation MoCA-B score is 16; taVNS stimulation MoCA-B score is 18; we estimate that the sham group MoCA-B score is 14 and the combined stimulation group MoCA-B score is 22. The target effect size is with 80% power (β = 0.20) and a type I error of 5% (α = 0.05). Considering a dropout rate of 10%, a total of 88 participants is necessary. In this study, we intend to recruit 88 participants, with 22 participants in each group.

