### Statistical methods

In this study, statistical analyses will be conducted using IBM SPSS Statistics 26. We will follow the intention-to-treat (ITT) principle for the primary analysis. For participants with partially missing outcome data (e.g., missed follow-up assessments), we will apply multiple imputation using chained equations under the assumption of data missing at random (MAR). Sensitivity analyses will be conducted using both complete-case analysis and per-protocol sets to assess robustness. Given the inclusion of multiple secondary outcomes (RBMT, MBI, P300 latency/amplitude), we will apply Bonferroni correction to adjust for multiple testing. Specifically, the significance threshold for secondary outcomes will be set as 0.0125. The study employs a 2 × 2 factorial design with rTMS (yes/no) and taVNS (yes/no) as independent factors. To examine the main effects and interaction effects of rTMS and taVNS on outcomes, we will use two-way repeated-measures ANOVA or mixed-effects models, depending on the distribution and structure of the data. For longitudinal outcomes measured at T0, T1, and T2, we will fit linear mixed-effects models (LMMs) with fixed effects for group, time, and their interaction, and a random intercept for participants to account for within-subject correlation. Additionally, we will explore including baseline covariates such as age, sex, and baseline cognitive score (e.g., baseline MoCA-B) in the models to improve precision and control for potential confounding. A *P* < 0.05 will be considered statistically significant.

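### The only within-patient term named for the T0/T1/T2 model is a random intercept, so single-visit change contrasts share one pooled standard error that is biased unless the between-visit differences have equal variance

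*Protocol article*

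**What the plan says.** The Statistical methods section of the protocol article sets the longitudinal analysis in one sentence. It covers all three visits ("For longitudinal outcomes measured at T0, T1, and T2") and continues: "we will fit linear mixed-effects models (LMMs) with fixed effects for group, time, and their interaction", together with "a random intercept for participants to account for within-subject correlation". No residual covariance structure, random slope, robust standard error or sphericity correction is named.

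For the factorial effects of rTMS and taVNS, the same section leaves the model class open: "we will use two-way repeated-measures ANOVA or mixed-effects models, depending on the distribution and structure of the data". Missing outcomes are to be filled by multiple imputation, so the analysed data sets will be balanced over visits. Covariates, including baseline MoCA-B, are to be explored.

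The visits are set out under Neuropsychological assessment: "The assessments will be performed at baseline, 4-week treatment, and 4-week post-treatment follow-up". T0–T1 and T1–T2 are therefore each about 4 weeks apart and T0–T2 about 8 weeks.

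**The concern.** A random intercept with independent residuals implies one variance at all visits and one correlation for all pairs of visits. This design gives reasons to doubt that. T0 precedes treatment while T1 and T2 follow it, and T0–T2 spans twice the interval of the other two pairs. If correlation falls with time, or if the two post-baseline visits resemble each other more than either resembles baseline, the T2–T0 change has the largest (or joint largest) variance of the three differences. The model nevertheless gives it the average.

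At stake is the reading of any single-visit contrast from the group-by-time model. A standard error that is too small at T2 would make an effect at follow-up look better supported than it is. One that is too large at T1 would lose power at the end of treatment. The same applies at the 0.0125 threshold for secondary outcomes.

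**Working it through.** **Figure in the plan.** The plan states no figure for this point. The sample size of 88 (22 per group) uses no repeated-measures term, and no SD is given, so it neither tests the covariance choice nor depends on it. About 20 evaluable patients per arm follow from 10% dropout (22 × 0.9 = 19.8).

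**Inputs.** From the protocol: four equal arms, three visits, α = 0.05. Assumed: two-sided tests, complete data, no true effect, and the visit correlations and SD ratios below.

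**Formula.** Let V(jk) be the variance of the within-patient difference between visits j and k: V(jk) = s_j² + s_k² − 2·r_jk·s_j·s_k. For data balanced over visits, the random-intercept model uses the mean of V(01), V(02) and V(12) for every change contrast. Hence:

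- model SE / true SE = √(mean V / V for that pair)
- type I error ≈ 2·[1 − Φ(1.96 × ratio)]

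**Worked example**, correlations T0–T1 / T0–T2 / T1–T2 = 0.75 / 0.65 / 0.80, SDs equal to 1. V(01) = 2(1 − 0.75) = 0.50, V(02) = 0.70, V(12) = 0.40, and the mean is 1.60/3 = 0.533. At T2 the ratio is √(0.533/0.70) = 0.873, giving 8.7%. At T1 it is √(0.533/0.50) = 1.033, giving 4.3%.

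| Assumed pattern (T0–T1 / T0–T2 / T1–T2) | V(01), V(02), V(12) | T1–T0: ratio, type I | T2–T0: ratio, type I |
|---|---|---|---|
| A. 0.75/0.65/0.80, equal SD | 0.50, 0.70, 0.40 | 1.033, 4.3% | 0.873, 8.7% |
| B. 0.80/0.64/0.80, equal SD | 0.40, 0.72, 0.40 | 1.125, 2.7% | 0.839, 10.0% |
| C. 0.65/0.65/0.85, equal SD | 0.70, 0.70, 0.30 | 0.900, 7.8% | 0.900, 7.8% |
| D. 0.70/0.65/0.80, post-baseline SD ×1.2 | 0.76, 0.88, 0.576 | 0.986, 5.3% | 0.916, 7.3% |
| E. 0.70/0.60/0.80, equal SD | 0.60, 0.80, 0.40 | 1.000, 5.0% | 0.866, 9.0% |
| F. 0.70/0.68/0.75, equal SD (mild) | 0.60, 0.64, 0.50 | 0.983, 5.4% | 0.952, 6.2% |
| G. 0.70 throughout, post-baseline SD ×1.25 | 0.8125, 0.8125, 0.9375 | 1.025, 4.5% | 1.025, 4.5% |
| H. 0.73/0.78/0.78, SDs 1.00/1.10/1.22 | 0.60, 0.60, 0.60 (before rounding) | 1.000, 5.0% | 1.000, 5.0% |

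Pattern H has unequal variances and unequal correlations, yet its standard errors are correct. The condition that matters is equal variance of the differences (sphericity), which is weaker than full compound symmetry.

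**Simulation** (4 × 20, 20,000 null trials). For patterns A to D, the T2–T0 contrast rejected in 8.9%, 9.9%, 7.7% and 7.1% of trials. With a visit-specific variance, as an unstructured covariance supplies, rejection was 4.9–5.3%.

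**Omnibus tests** under the random-intercept model, same four patterns: group × time 5.7%, 5.8%, 6.1% and 5.1%; rTMS × taVNS × time 5.5%, 5.6%, 5.8% and 5.1%. Pooling over visits averages most of the error out.

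**Secondary threshold.** At 0.0125 (critical value 2.498), T2 ratios of 0.873 and 0.839 give about 2.9% and 3.6%.

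**The case against.** The strongest reply has four parts.

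1. *The protocol names no T1–T0 or T2–T0 contrast as its efficacy test.* A reader might infer that the trial's main tests run at up to 10%. The document does not support that. It names group, time, their interaction, and the factorial main and interaction effects; the Outcomes section fixes no primary time point. For the omnibus interaction the error is about 5–6%. This stands and limits the point to single-visit contrasts, which are nevertheless the natural way to interpret an interaction over three visits.

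2. *The condition and direction are easy to overstate.* A reader might infer that both standard errors are wrong unless all variances and correlations are equal, or that T2 is always understated. Neither is true: pattern H breaks compound symmetry harmlessly, pattern E affects only T2, and pattern G is slightly conservative at both visits. Greater variance after treatment is therefore not a strong argument by itself. This stands.

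3. *The article does not exclude other covariance terms.* A full analysis plan could add a residual structure, so it goes too far to say that the protocol rules everything else out. But this is not a silent text: it states a method and gives the random intercept the job of handling within-patient correlation. The open choice of repeated-measures ANOVA does not help, because univariate ANOVA without a sphericity correction shares the weakness.

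4. *If baseline became a covariate and T0 left the outcome vector, only one correlation would remain.* That is true, but the stated model covers T0, T1 and T2, and the covariates are exploratory.

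A random intercept for three visits is also conventional. That makes the choice common; it does not make its standard errors right for single-visit contrasts.

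**Conclusion.** The point holds in limited form. As written, the model gives one pooled standard error to every change-from-baseline group contrast, and that error is biased at T1, T2 or both unless the between-visit differences have equal variance. Under assumed correlations that decay with time or are higher between T1 and T2, the nominal 5% becomes about 7–10% for T2–T0 and about 3–8% for T1–T0. With milder decay (pattern F) T2–T0 is near 6%. Omnibus tests stay near 5–6%, and larger post-baseline variance alone leaves the level at about 4.5%.

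These sizes rest on 20 evaluable patients per arm, data balanced over visits, two-sided tests and visit correlations that the protocol does not give. The design makes decay plausible but does not establish it. This is a cheap improvement; it does not invalidate the plan.

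**What to change.** In Statistical methods, replace the random intercept with an unstructured 3 × 3 within-patient covariance across T0, T1 and T2. In the named software this is SPSS MIXED with the REPEATED subcommand and COVTYPE(UN), without a separate random intercept, and with Satterthwaite degrees of freedom. Keep the random-intercept model only as the stated fallback if the unstructured model does not converge.

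If repeated-measures ANOVA is used instead, apply a sphericity correction to the omnibus tests and contrast-specific error terms to the single-visit contrasts. The omnibus correction does not repair the contrasts.

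Cost: one or two sentences, no new data and no change to the 88 participants. The unstructured matrix has 6 covariance parameters against 2 (intercept and residual variance). With 80 evaluable patients in four arms, the degrees of freedom fall from about 2 × (80 − 4) = 152 to about 80 − 4 = 76, and the critical t rises from 1.98 to 1.99.

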### Demographic data collection

Demographic characteristics of all participants including age, gender, educational level, as well as medical history, medication list, and comorbidities will be documented.

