### Outcomes

The primary outcome is the MoCA-B score. Secondary outcomes include RBMT, MBI, P300 latency and amplitude. Any adverse events occurring during the intervention period, such as dizziness, pain, skin redness, and itchiness, will be reported by research assistants and managed by experienced physicians. We will assess the causality between adverse events and the treatment, as well as the severity of the adverse events. Serious adverse events will be reported to the ethics committee.

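### Baseline MoCA-B, offered as an optional covariate in a model that already has T0 as a response, adds no precision to the group-by-time effect; a baseline-adjusted T1/T2 model would

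*Protocol article*

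**What the plan says.** All the relevant statements are in the protocol article. The Outcomes section states: "The primary outcome is the MoCA-B score". Under Statistical methods, the repeated measurements are handled as follows: "For longitudinal outcomes measured at T0, T1, and T2, we will fit linear mixed-effects models", with "fixed effects for group, time, and their interaction, and a random intercept for participants to account for within-subject correlation". T0 is therefore listed among the modelled responses. On covariates, the same section says "we will explore including baseline covariates such as age, sex, and baseline cognitive score (e.g., baseline MoCA-B) in the models", and gives the purpose as "to improve precision and control for potential confounding".

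The section does not name a model with only T1 and T2 as responses, a baseline-by-time term, or a constraint of equal arm means at T0. Main effects and the interaction of rTMS and taVNS are to be examined by "two-way repeated-measures ANOVA or mixed-effects models, depending on the distribution and structure of the data".

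**The concern.** With T0 in the response and a group-by-time interaction in the model, the treatment effect is how far the arms diverge after T0. That is a within-participant contrast. Baseline MoCA-B is constant within a participant, so as a main effect it explains differences between participants, and the contrast has already removed those. For MoCA-B, the stated aim of better precision is then not met where it matters.

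What is at stake is efficiency. Baseline MoCA-B is collected on everyone, and with 22 randomised per arm and 10% expected dropout, the trial has reason to use it fully. A change-from-baseline comparison uses it less well than an adjusted comparison does.

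**Working it through.** **Inputs from the protocol.** Sample size section: assumed MoCA-B means of 14 (sham), 16 (rTMS), 18 (taVNS) and 22 (combined); α 0.05; power 80%; dropout 10%; 88 in total, 22 per group. Statistical methods section: the model described above.

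**Inputs assumed.** The within-participant correlation ρ and the SD; the document gives neither. Compound symmetry follows from the random intercept.

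**The plan's own figure.** Without an SD or effect size, the total of 88 can be neither reproduced nor refuted. The means imply:
- rTMS main effect: (16+22)/2 − (14+18)/2 = 3
- taVNS main effect: (18+22)/2 − (14+16)/2 = 5
- interaction: 22 − 16 − 18 + 14 = 2

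Evaluable participants per arm: 22 × 0.9 = 19.8, taken as 20. With 20 per arm, the 3-point rTMS effect has 80% power if the SD is 4.73. That SD is solved backwards from the power target and serves only as an illustration.

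**Step 1: the covariate cancels.** For participant i at visit t, write the planned model plus γ × baseline_i. The T1 group-by-time contrast is (mean T1 − mean T0) in one arm minus the same difference in the other. The term γ × baseline_i is present at both visits and drops out of each difference.

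A simulation confirms this (80 participants, four arms, assumed SD 4, 60 runs at each ρ). Adding baseline changed the group-by-time estimates by less than 1e-12. Mean standard errors for the rTMS × taVNS × T1 contrast were:

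| ρ | T0–T2 model | same, plus baseline | T1/T2 model adjusted for baseline |
|---|---|---|---|
| 0.3 | 2.100 | 2.093 | 1.717 |
| 0.5 | 1.742 | 1.740 | 1.522 |
| 0.7 | 1.391 | 1.391 | 1.290 |

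The slight drops between the first two models come from runs in which the random-intercept variance was estimated as zero. The actual spread of the estimates did not change. The third model's standard error is 18%, 13% and 7% smaller than the first's.

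**Step 2: size of the loss.** Per-participant variance of the T1 contrast:
- planned model (change from baseline): 2(1 − ρ)SD²
- baseline-adjusted: (1 − ρ²)SD²
- ratio: 2(1 − ρ) / [(1 − ρ)(1 + ρ)] = 2/(1 + ρ)

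This gives 1.33, 1.25, 1.18 and 1.11 at ρ of 0.5, 0.6, 0.7 and 0.8.

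**Step 3: illustration in power.** A main effect compares 40 with 40, so its SE is √(variance/20). With SD 4.73 (SD² = 22.37), a 3-point effect and a two-sided 5% test:

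| ρ | SE, planned | power | SE, adjusted | power |
|---|---|---|---|---|
| 0.5 | √(1.00 × 22.37/20) = 1.058 | 80% | √(0.75 × 22.37/20) = 0.916 | 90% |
| 0.6 | √(0.80 × 22.37/20) = 0.946 | 88% | √(0.64 × 22.37/20) = 0.846 | 94% |

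**The case against.** The strongest reply is that adding no precision is true only within limits. It is exact for group-by-time, with complete data and baseline as a main effect only. The protocol does not label group-by-time as its estimand. Other contrasts from the same model do respond: at ρ 0.5, the variance of the simple group difference at T1 is 0.78 SD² with the covariate against 1.00 SD² without. This stands as a limit on the point. It does not remove it, because neither the simple T1 difference nor the time-averaged group effect is named as the target, and the latter is diluted by T0.

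A second reply is that the article gives no model equation, so a baseline-by-time term or equal T0 means could still be adopted; either would recover the gain. That is fair, but the text as written puts T0 in the response and mentions neither. For RBMT, MBI and P300, baseline MoCA-B is not the outcome's own baseline, so the overlap between response and covariate concerns MoCA-B only.

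A reader might also infer that leaving the adjustment open biases the primary P value. For group-by-time this does not follow: adding baseline moves neither the estimate nor its true precision, so there is no gain to be had from choosing. The analysts are also to be blinded to allocation. Nor do the documents show that the trial is underpowered. They state no SD, and at the illustrative SD the planned contrast still reaches the 80% target at ρ 0.5 and 0.6.

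**Conclusion.** The point holds for the group-by-time effect on MoCA-B. As described, the baseline covariate does not deliver the precision it is meant to bring, and the planned analysis has a T1 variance 11% to 33% larger than a baseline-adjusted one for ρ between 0.8 and 0.5. The loss shrinks as ρ approaches 1. These figures rest on compound symmetry, complete data and an assumed ρ; the power figures rest also on the assumed SD of 4.73 and apply to the rTMS main effect only, not to the synergy hypothesis.

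This is a matter of efficiency. The planned mixed model is a valid analysis, and having T0 as a response is not an error in itself. The change is worth making because a better use of the same data is available.

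**What to change.** Replace the exploratory wording for baseline MoCA-B with one fixed specification of the primary MoCA-B model, either:

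- T1 and T2 as responses, with T0 MoCA-B as a mandatory covariate and a baseline-by-visit term; or
- T0, T1 and T2 as responses, with arm means constrained equal at T0 and no baseline covariate.

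In both, include rTMS, taVNS, their interaction, and the interactions of these with visit. Age, sex and education can remain optional; no calculation here supports making them mandatory.

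The cost is a change of wording in the protocol or analysis plan. MoCA-B is already measured at baseline, so no extra participants or data are needed.

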### ERP-P300

Data processing will be conducted using MATLAB R2022b. The EEG raw data preprocessing will be performed using the EEGLAB toolbox. The preprocessing steps mainly include: localizing electrodes, removing unused electrodes, referencing, filtering, segmenting, and baseline correcting the data, as well as removing artifacts and performing independent component analysis (ICA) (Zhuang et al., 2023). After preprocessing the ERP data, the amplitude and latency of the P300 wave will be analyzed at the Fz, Cz, and Pz electrodes.

The significance level for statistical analysis will be set at 5% (*P* < 0.05). The researchers conducting the data analysis will be blinded to the allocation and interventions.

### Ethics and dissemination

This study protocol has been approved by the Ethics Review Committee of Shanghai Tongren Hospital (No. 2021-047-01). Study-related information will be provided by the Rehabilitation Department of Shanghai Tongren Hospital. The purpose, objectives, inclusion criteria, and procedures of the research will be explained in detail. The research team will offer face-to-face consultations to all potential participants and their guardians to address any questions they may have prior to signing the informed consent forms. Written informed consent will be obtained from all participants. Participants are allowed to withdraw from the study at any time, and reasons for withdrawal will be documented. The results of this study will be published in peer-reviewed journals.

## Discussion

In this study, we intend to investigate the effects of combined rTMS and taVNS on MCI patients. Our study is designed as a randomized controlled trial aiming to evaluate the effectiveness and safety of this combined therapeutic approach in improving cognitive functions.

RTMS is a non-invasive brain stimulation technique that has been extensively studied in recent years for its potential to improve cognitive function. Based on the recommendations of the International Federation of Clinical Neurophysiology (IFCN) guidelines (2014-2018) (Lefaucheur et al., 2020), we selected 10 Hz rTMS targeting the left DLPFC as the stimulation protocol for this study. The selection of parameters in this study is also supported by findings from high-quality clinical research. Research has shown that high-frequency rTMS can enhance memory function in elderly MCI patients (Drumond Marra et al., 2015). A meta-analysis study revealed that stimulating the DLPFC with 10 Hz can significantly improve cognitive function in MCI patients (Licht et al., 2023; Xie et al., 2021). RTMS promotes the recovery of cognitive function by altering cortical excitability, modulating neural plasticity, and facilitating neural network reorganization (Zhang et al., 2022).

TaVNS has been utilized to enhance cognitive function as a potential non-invasive therapeutic approach. Research indicates that taVNS can enhance cognitive function by modulating the activity of both the autonomic nervous system and the central nervous system (Kang et al., 2024). TaVNS can improve cognitive performance in patients with MCI, and such improvements can persist for a period of time after the intervention has ended (Wang et al., 2022). In addition, the effects of taVNS in improving cardiovascular function and regulating the autonomic nervous system have also been confirmed, which may further support its underlying mechanisms in enhancing cognitive function (Antonino et al., 2017). Given the current lack of standardized stimulation parameters for taVNS in improving MCI, this study referenced prior literature (Wang et al., 2022; Yao et al., 2022) to adopt parameters that balance neuromodulatory efficacy and safety. Should preliminary or formal studies reveal suboptimal parameter efficacy, we will conduct additional parameter-screening trials to compare the differential effects of various pulse width and frequency combinations. Future research must further delve into the optimization of taVNS stimulation parameters.

The P300 component of event-related potentials (ERPs) serves as a crucial indicator in cognitive neuroscience research. It is widely utilized to assess attention and cognitive processing (Asaumi et al., 2014). The P300 is typically elicited through the oddball paradigm. The latency of the P300 is related to the time taken for stimulus evaluation and response preparation. The amplitude of the P300 is associated with the amount of attentional resources invested in the task (Raggi et al., 2024). Research indicates that significant changes in the latency and amplitude of the P300 are observed in patients with MCI and Alzheimer’s Disease (AD), which are associated with pathological aging and cognitive impairment (Paitel et al., 2021). Intervening in patients with MCI through rTMS may lead to improvements in the latency and amplitude of the P300, thereby reflecting an enhancement in cognitive function (Chen et al., 2024). TaVNS failed to significantly modulate the latency and amplitude of the P300 in healthy volunteers, which may be attributed to insufficient stimulation parameters or too short a stimulation duration (Gadeyne et al., 2022). Further research is still required in the future to verify its therapeutic effects.

The innovation of this study lies in the first-time application of combining rTMS with taVNS in patients with MCI. We hypothesize that this dual intervention may synergistically amplify the therapeutic effects through both top-down and bottom-up mechanisms.

However, this study also has some limitations. Firstly, the relatively small sample size may limit the generalizability of the results. Additionally, although we employed a double-blind design, there may still be a risk of unblinding due to technical reasons. Future research should consider increasing the sample size and further exploring the impact of different stimulation parameters on the therapeutic effects.

In conclusion, this study will provide preliminary evidence for the application of combined rTMS and taVNS in patients with MCI. This will offer important theoretical foundations and practical guidance for the development of more effective treatment strategies for MCI.
